# Study protocol for safety and efficacy of all-oral shortened regimens for multidrug-resistant tuberculosis: a multicenter randomized withdrawal trial and a single-arm trial [SEAL-MDR]

**DOI:** 10.1186/s12879-023-08644-8

**Published:** 2023-11-27

**Keywords:** Multidrug-resistant, Tuberculosis, Efficacy, Safety, Trial

## Abstract

**Introduction:**

The urgent need for new treatments for multidrug-resistant tuberculosis (MDR-TB) and pre-extensively drug-resistant tuberculosis (pre-XDR-TB) is evident. However, the classic randomized controlled trial (RCT) approach faces ethical and practical constraints, making alternative research designs and treatment strategies necessary, such as single-arm trials and host-directed therapies (HDTs).

**Methods:**

Our study adopts a randomized withdrawal trial design for MDR-TB to maximize resource allocation and better mimic real-world conditions. Patients’ treatment regimens are initially based on drug resistance profiles and patient’s preference, and later, treatment-responsive cases are randomized to different treatment durations. Alongside, a single-arm trial is being conducted to evaluate the potential of sulfasalazine (SASP) as an HDT for pre-XDR-TB, as well as another short-course regimen without HDT for pre-XDR-TB. Both approaches account for the limitations in second-line anti-TB drug resistance testing in various regions.

**Discussion:**

Although our study designs may lack the internal validity commonly associated with RCTs, they offer advantages in external validity, feasibility, and ethical appropriateness. These designs align with real-world clinical settings and also open doors for exploring alternative treatments like SASP for tackling drug-resistant TB forms. Ultimately, our research aims to strike a balance between scientific rigor and practical utility, offering valuable insights into treating MDR-TB and pre-XDR-TB in a challenging global health landscape. In summary, our study employs innovative trial designs and treatment strategies to address the complexities of treating drug-resistant TB, fulfilling a critical gap between ideal clinical trials and the reality of constrained resources and ethical considerations.

**Trail registration:**

Chictr.org.cn, ChiCTR2100045930. Registered on April 29, 2021.

**Supplementary Information:**

The online version contains supplementary material available at 10.1186/s12879-023-08644-8.

## Introduction

Tuberculosis (TB) remains a pressing global health issue with substantial mortality [1, 2]. The emergence of multidrug-resistant (MDR-TB) and pre-extensive drug-resistant TB (pre-XDR-TB) exacerbates the problem, contributing to significant morbidity [3, 4], mortality (30–50%) [5, 6], and economic burden. Globally, approximately 500,000 MDR/RR-TB cases arise annually, with pre-XDR-TB constituting around 26% of this number [3].

Recent individual patient data (IPD) meta-analysis points to the efficacy of specific second-line drugs like linezolid (Lzd), fluoroquinolones (FQs), bedaquiline (Bdq), clofazimine (Cfz), and others in treating MDR-TB [7]. WHO and other agencies have subsequently devised treatment guidelines that categorize these second-line drugs into three groups (A, B, C), based on their efficacy and safety [8, 9]. For example, The 2020 and 2022 WHO guidelines, favor a 6-month regimen of Bdq, pretomanid (Ptm), Lzd, and moxifloxacin (Mfx) (BPaLM), or a 9-month regimen of seven drugs, over conventional 18-month individualized regimens [10, 11]. Despite these advancements, evidence for modifying WHO-recommended short regimens is limited, underscoring the need for tailored, shorter treatment protocols for MDR-TB that are grounded in local clinical realities and evidence-based decision-making [12].

China, an upper-middle-income country, bears a significant MDR-TB burden but lacks comprehensive studies addressing these issues [13]. China has the world’s second-largest MDR/RR-TB population, with 33,000 new cases in 2021 and a treatment success rate of only 53%, below the global average of 60% [1]. Our previous multicenter cohort study demonstrated the efficacy of three 9-month, all-oral regimens in treating MDR-TB and pre-XDR-TB, significantly improving the treatment course and outcomes [14]. Regimen A (Bdq + Lzd + Mfx + Cs + Pza) and Regimen B (Lzd + Mfx + Cs + Cfz + Pza) served as treatments for MDR-TB patients, allocated to Groups A and B based on patient preference. Meanwhile, Regimen C (Bdq + Lzd + Cs + Cfz + Pza) was designated for pre-XDR-TB patients. In addition to these conventional chemotherapies, our team has focused on a host-directed therapy, salazosulfapyridine (SASP). Regimen D (Lzd + Cs + Cfz + Pza + SASP) had a satisfactory efficacy and safety for pre-XDR-TB treatment (not published yet).

Building on our prior work, we aim to conduct a randomized controlled trial to further optimize treatment durations without revisiting drug combinations. This study protocol (date 2022-07-01, version 1.5) outlines our methodology for achieving this goal.

## Methods

### Trial design and oversight

We are conducting a two-part, patient-stratified, treatment-response-guided study: a randomized withdrawal trial for MDR-TB and a single-arm trial for pre-XDR-TB (Fig. 1; Table 1). For MDR-TB, patients are assigned to either Regimen A (Bdq, Lzd, Mfx, Cs) or Regimen B (Lzd, Mfx, Cs, Cfz, Pza) based on treatment preference and FQ drug susceptibility tests (DST). Compared to our previous study, Pza is deleted from Regimen A. For pre-XDR-TB, we employ Regimen C (Bdq, Lzd, Cs, Cfz, Pza) and Regimen D (Lzd, Cs, Cfz, Pza, SASP). Each regimen lasts 6–9 months. Post-6 months, participants in Groups A and B are subdivided into 6-month and 9-month treatment durations based on randomization, while those in Groups C and D are similarly divided based on clinical judgment. For the randomized withdrawal trial, the primary hypothesis is that the 6-month regimen will be non-inferior to the 9-month regimen in terms of unfavorable outcomes.

**Fig. 1 Fig1:**
[figure not shown]
The flow diagram of the SEAL-MDR study. The diagram outlines the key steps in the study, starting with patient recruitment, followed by initial selection of treatment regimens based on *M. tuberculosis* drug resistance spectrum and patient preferences. For the randomized withdrawal trial, patients with a favorable treatment response will be randomized to 6 or 9 months of treatment after 6 months of treatment. Participants with a poor treatment response will not be randomized but will continue on a 9-month treatment regimen. In the single-arm trial, participants with a favorable response will stop treatment at month 6, otherwise treatment will be extended to 9 months. Throughout the study, FQ resistance results may be obtained at various stages to guide initial and subsequent regimen adjustments. Participants will attend visits at 12 months post-treatment to obtain primary and secondary endpoints. (Abbreviations in this figure: Bdq: bedaquiline; Cfz: clofazimine; DST: Drug susceptibility testing; FQ: fluoroquinolone; Lzd: linezolid; Mfx: moxifloxacin; Pza: Pyrazinamide; Rif: rifampicin; SASP: Sulfasalazine; TB: tuberculosis)

**Table 1 Tab1:** Trial regimens

FQ susceptibility	Regimen	Drugs	Durations
MDR-TB	A	bedaquiline, linezolid, moxifloxacin, cycloserine and pyrazinamide	6–9 months
	B	linezolid, moxifloxacin, cycloserine, clofazimine and pyrazinamide	6–9 months
Pre-XDR-TB	C	bedaquiline, linezolid, cycloserine, clofazimine and pyrazinamide	6–9 months
	D	linezolid, cycloserine, clofazimine, pyrazinamide and salazosulfapyridine	6–9 months

This study, named SEAL-MDR, was registered with the Chinese Clinical Trials Registry and has received ethical approval from participating hospitals. Written informed consent will be obtained from all adult participants or their legal guardians by trained medical personnel who may be an investigator, clinician, or designated nurse experienced in explaining the elements of clinical trials.

### Study sites

Trial sites should have adequate staffing, facilities, and recruitment capabilities. They must also have access to quality-assured laboratories capable of performing required tests and have secure data management systems in place. Thirty-two sub-centers are participating, with competitive enrollment until required sample sizes are met (Table S8). The four treatment regimen groups A-D may be unevenly distributed in each sub-center, and competitive enrollment is used in this clinical trial until the sample size meets the requirements for each group.

### Selection of participants

Eligible participants are 15–75 years old with confirmed pulmonary MDR-TB or pre-XDR-TB, subject to exclusion criteria, which include QTcF ≥ 450 ms, HIV positivity, known drug allergies, and abnormal lab values among others. Full inclusion and exclusion criteria are outlined in Table S1.

Before trial-specific procedures, eligible patients are given comprehensive information, including known risks and potential benefits such as reduced treatment duration and costs. Consent is documented, and screening logs are securely maintained.

### Confirmation of MDR/Pre-XDR-TB

DST is a key prerequisite for trial entry, with varying methodologies dependent on local lab capabilities. Mandatory DST results are required for rifampicin, isoniazid, and FQs. Other study drugs like Bdq, Lzd, Cfz, and Pza are not obligatory for DST. Patients with resistance to these non-mandatory drugs are excluded from the study.

For DST, rifampicin resistance is confirmed using the Xpert MTB/RIF assay (Cepheid, USA), while susceptibility to FQs, isoniazid, and ethambutol is determined either through genotypic (gDST) or phenotypic (pDST) assays measuring minimum inhibitory concentration (MIC) (Thermo Scientific, USA), with genotypic methods including PCR melting curve analysis (Zeesan Biotech, China), whole-genome sequencing (Novogene, China), and mass spectrometry (Conlight Medical, China).

### Randomization, enrolment and follow-up

Before initiating treatment, all available DST results (e.g., Xpert, gDST, pDST) are employed to triage patients with MDR-TB and pre-XDR-TB. Considering variables such as regimen affordability and past adherence, MDR-TB patients are allocated to either Regimen A or B (Table 1). Regimen B is preferred for uninsured participants, those concerned about drug costs, and individuals willing to accept potential skin discoloration caused by Cfz. Pre-XDR-TB patients are allocated to either Regimen C or D, with Regimen D being better suited for those without insurance coverage and lesser financial means.

Should post-entry DST results confirm resistance to any study drug, treatment regimens will be adjusted according to established clinical practice principles in our previous studies [1]. For example, If initial gDST is unavailable and later pDST reveals FQ resistance 2–3 months post-enrollment, participants will transition from Regimens A/B to C/D, incorporating the prior treatment duration into the revised 6-month course. In certain scenarios, participant withdrawal may be necessitated. For example, participants unwilling to switch sill be prescribed long-course treatment and excluded from the study.

Participants initially undergo a 6-month treatment course. A blinded mid-point review committee evaluates clinical events and favorable treatment responses during the sixth-month visit (FR-6, Table S2). This assessment includes sputum culture conversion at month four, adequate drug intake at month six (excluding those who received less than ~ 90% of study doses), and chest computed tomography (CT) stabilization. Participants having a FR-6 will be centrally randomized into either a 6- or 9-month treatment group via MedSci RTSM Cloud Platform (rtsm.medsci.cn). Otherwise, they will continue their current regimen until month nine. Failure to convert by the eighth month necessitates an extension to an 18–20 month regimen, marking it as a treatment failure.

Participants attend baseline screenings, bi-weekly visits for the first two months, monthly visits until treatment completion, and quarterly check-ups during a 12-month post-treatment period (Tables S3 and S4). The screening procedures include medical history, physical examination, vision tests, peripheral neuropathy screening, psychological assessments, and the collection of various samples for testing. CT scans are preferred over X-rays for assessing lung lesions, which is a routine at the study sites.

Upon passing the screening, eligible participants are enrolled, registered offline, and assigned a treatment regimen by an authorized researcher at each sub-center. These assignments are re-verified by the Central Coordination and Quality Control Group (CCQCG) at Shenzhen Third People’s Hospital.

Effectiveness and safety metrics are evaluated at each follow-up visit through symptom checklists, clinical exams, and ongoing diagnostic tests. Grade 3 or 4 clinical and laboratory adverse events (AEs) are defined per the DAIDS AE Grading Table [12]. Chest CT scans are regularly updated and reviewed blindly by two independent experts using a standardized approach (Table S2). An endpoint review committee examines unfavorable clinical outcomes like treatment failure, TB recurrence, or death. Adherence metrics and educational counseling are also provided, along with psychological support through WeChat and telephone channels. Post-treatment, successfully treated cases will be monitored for 12 months to assess any TB recurrence.

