### Treatment of patients

Details of the drug combinations and duration for each of the Regimens A-D are shown in Table 1. Table 2 provides details on the drug types and dosages included in each regimen. In case of grade 3 or 4 AE triggered by Lzd, the Lzd dose was cut to 300 mg or ceased entirely as required. The rest of the five drugs, Bdq included, were given throughout the course of the treatment. All medications used in the study have received approval from the National Medical Products Administration and are prescribed solely by authorized study physicians at the respective research sites. None of the medications are provided free of charge. Contrary to employing the Directly Observed Treatment (DOT) strategy, this study designates a clinic staff member to oversee each patient’s treatment. This individual is tasked with verifying medication consumption, documenting it on the treatment card, and providing guidance to ensure proper administration and patient adherence.

**Table 2 Tab2:** Trial regimen drugs and doses

Drug	Weight group		Usage
	≤ 50 kg	> 50 kg	
Bedaquiline	400 mg daily for 2 weeks followed by 200 mg three times a week		Once, with meal
Linezolid	600 mg daily		Once, before or after meal
Moxifloxacin	400 mg daily		Once, before or after meal
Levofloxacin	500 mg daily	750 mg daily	Once, before or after meal
Cycloserine	500 mg daily	750 mg daily	Divided in two doses, before or after meal
Clofazimine	100 mg daily		Once, with meal
Pyrazinamide	1500 mg daily		Once, before or after meal
Sulfasalazine	3000 mg daily		Divided in three doses, with meal

Based on our prior cohort study experience and international guidelines, we have formulated a manual for the management of adverse reactions to second-line anti-TB drugs for the SEAL-MDR study (Table S5). Management of treatment interruptions was shown in Table S6.

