### Outcome measures

In this study, outcomes are categorized at the end of a 12-month post-treatment follow-up. Participants fall into one of three categories: unfavorable outcome, favorable outcome, or not assessable - the latter are excluded from the primary analysis (Table S7). The primary efficacy outcome, determined 15 months after initial assignment, includes treatment failure, loss to follow-up, or death from any cause. Treatment failure is a multifaceted term, defined by the end-point review committee, and encompasses lack of clinical and/or bacteriological response, adverse drug reactions that induced regimen adjustments, or newly identified drug resistance. Specifically, bacteriologic failure is defined by the presence of two genetically identical, *M. tuberculosis*-culture-positive sputum samples within the month 8 visit window. Bacteriologic relapse and reinfection refer to a positive test for a genetically identical or different *M. tuberculosis* strain, respectively, within 12 months post-treatment. In cases where strain genotyping is not feasible, the term ‘bacteriologic recurrence’ is employed. Secondary efficacy outcomes include unfavorable status at 21 months post-assignment, end-of-treatment success, culture conversion by month 2, time to sputum culture-negative status in liquid media, and favorable treatment response at FR-6. Safety outcomes involve the occurrence of AEs graded ≥ 3 or serious AEs of any grade within 6–9 months of treatment initiation, as per the DAIDS AE Grading Table [15]. Clofazimine-induced skin discoloration is also specifically documented (Table S2).

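### As worded, linezolid stopped late for toxicity counts as treatment failure yet need not prevent month-6 randomization, so failures that duration cannot affect may enter the primary comparison

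*Protocol article*

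**What the plan says.** Five parts of the protocol article bear on this.

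- **Permitted linezolid change (Treatment of patients).** "In case of grade 3 or 4 AE triggered by Lzd, the Lzd dose was cut to 300 mg or ceased entirely as required". The next sentence has the remaining drugs carry on: "The rest of the five drugs, Bdq included, were given throughout the course of the treatment".
- **Treatment failure (Outcome measures).** "Treatment failure is a multifaceted term, defined by the end-point review committee", and it "encompasses lack of clinical and/or bacteriological response, adverse drug reactions that induced regimen adjustments, or newly identified drug resistance". Failure is part of the primary outcome, which is determined 15 months "after initial assignment, includes treatment failure, loss to follow-up, or death from any cause".
- **Assignment (Randomization, enrolment and follow-up).** At enrolment, "eligible participants are enrolled, registered offline, and assigned a treatment regimen by an authorized researcher at each sub-center". The duration arms are allocated later, at month 6.
- **Gate to randomization (same section).** "A blinded mid-point review committee evaluates clinical events and favorable treatment responses during the sixth-month visit". The items listed for a favorable response (FR-6) are culture conversion at month 4, "adequate drug intake at month six (excluding those who received less than ~ 90% of study doses"), and a stable chest CT. Those with FR-6 are randomized 1:1 to 6 or 9 months; the others stay on treatment to month 9.
- **Analysis set (Statistical analysis).** The mITT set, on which the analysis focuses, is everyone randomized and treated at least once.

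**The concern.** Read together, these rules let one person be a favorable responder at month 6 and already a primary-outcome failure. Stopping linezolid for toxicity is an adverse reaction that changed the regimen. Nothing in Outcome measures exempts it because Treatment of patients allows it, and no listed FR-6 item asks whether failure has already occurred.

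A failure fixed before randomization cannot depend on whether treatment then lasts 6 or 9 months. Randomization spreads such failures evenly over both arms, where they shrink the absolute difference. In a non-inferiority comparison this favors the shorter course: a real excess among participants whose outcome can still change is understated and more easily falls within the 15-point margin. Linezolid is in both Regimen A and Regimen B, so the whole randomized part is exposed.

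**Working it through.** **1. The plan's own sample size.** Inputs from Sample size calculation: 73% favorable in both arms, margin 15 points, one-sided 5%, power 80%, 20% drop-out, 90% FR-6.
n per duration arm = (1.645 + 0.842)² × 2 × 0.73 × 0.27 / 0.15² = 108.3, so 109; two arms 218; 218/0.8 = 272.5, so 273; 273/0.9 = 303.3, so **304**. The stated figure reproduces. Working back, 304 × 0.9 × 0.8 / 2 = 109.4 evaluable per duration arm in one regimen.

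**2. Does the intake item catch a late linezolid stop?** The article does not say whether doses are pooled over drugs, so both counts are shown. Planned doses over 182 days, from Table 2: bedaquiline 14 + 24 × 3 = 86; cycloserine 182 or 364 (once or twice daily counted); every other drug 182.

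| Regimen | Total planned doses | Pooled intake if linezolid stops at month 4 |
|---|---|---|
| A, four drugs (Trial design text) | 632 or 814 | 90.4% or 92.5% |
| A, five drugs (Table 1) | 814 or 996 | 92.5% or 93.9% |
| B | 910 or 1092 | 93.3% or 94.4% |

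Intake = 1 − (182 × 2/6)/total. Pooled, a stop at month 4 or later passes in every case. Counting linezolid alone, a month-4 stop gives 4/6 = 66.7% and fails; 90% is reached at 0.9 × 6 = month 5.4. Either count leaves a window. Dose reductions are left out of this arithmetic.

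**3. Does the per-protocol set remove them?** It requires more than 80% of planned treatment. For a 9-month participant (273 days; bedaquiline 14 + 37 × 3 = 125; totals 944 to 1638) who stops linezolid at month 4, pooled intake = 1 − (273 × 5/9)/total = 83.9% to 90.7%. On a pooled count, this threshold does not remove them.

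**4. Which clock?** Counted from enrolment, the secondary time point of 21 months equals 9 + 12, the end of follow-up after a 9-month course. Counted from month-6 randomization, planned follow-up ends at 0 + 12 = 12 months (6-month arm) or 3 + 12 = 15 months (9-month arm), so 21 months would overrun it. With assignment used for the regimen given at enrolment, the enrolment clock is the better reading, and months 0–6 lie inside the window.

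**5. Dilution.** Let f be the share of randomized participants already failed. The documents give no value, so f is assumed. Among the rest, take 27% unfavorable at 9 months and 42% at 6 months.
p9 = f + (1 − f) × 0.27; p6 = f + (1 − f) × 0.42; d = 0.15(1 − f); SE = √{[p9(1 − p9) + p6(1 − p6)]/109.4}; P(declare NI) = Φ((0.15 − d)/SE − 1.645).

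| f | d (points) | P(declare NI) |
|---|---|---|
| 0 | 15.0 | 5.0% |
| 1% | 14.85 | 5.2% |
| 3% | 14.55 | 5.8% |
| 5% | 14.25 | 6.3% |
| 10% | 13.5 | 7.8% |

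**6. How the dose count drives f.** Assume that 10–30% of otherwise eligible participants stop linezolid, evenly over six months. The passing window is (6 − 4)/6 = 0.33 pooled, giving f = 3.3–10% (P = 5.9–7.8%), or (6 − 5.4)/6 = 0.10 for linezolid alone, giving f = 1–3% (P = 5.2–5.8%).

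**7. Power when durations are truly equal.** If these failures come on top of the planned 27%, then p = f + (1 − f) × 0.27 in both arms and power = Φ(0.15/√(2p(1 − p)/109.4) − 1.645): 80.4% at f = 0, 77.7% at 5%, 75.6% at 10%. If the planned 27% already includes them, p stays at 0.27 and power stays at 80.4%.

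**The case against.** **Unseen material may settle it.** FR-6 is detailed in Table S2 and the outcome categories in Table S7, and neither is shown. The FR-6 list is introduced as non-exhaustive, and the mid-point committee also looks at clinical events. This stands as a condition on the finding. Still, no exclusion appears in the text, and the failure wording as printed conflicts with the permitted linezolid change.

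**A permitted stop may not be a regimen adjustment.** Elsewhere the article illustrates adjusting a regimen by a switch from A/B to C/D, and the end-point committee defines failure. A narrow reading is possible, but the printed phrase covers stopping a drug for toxicity. Leaving this to adjudication is a reason to write the rule down.

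**The clock may start at randomization.** For the 9-month arm, 3 + 12 = 15 months matches the primary time point exactly, whereas 15 months from enrolment is only 6 months after a 9-month course, although the same section categorizes outcomes at 12 months post-treatment. The text is therefore not clean. The 21-month time point nevertheless fits enrolment only.

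**The obvious remedy has a cost.** Adding a bar on prior failure to FR-6 would send culture converters with serious toxicity to nine months of treatment, because that is where participants without FR-6 go. This objection is right and shapes the fix below.

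**Stronger readings are tempting.** A reader might infer that type I error is inflated. It is not for the composite itself, which is compared validly as defined; what is understated is the difference among participants whose outcome duration can change. A reader might also infer a certain loss of power, but step 7 shows that this depends on what the planned 27% contains.

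**Conclusion.** The concern holds as a conditional, minor point about wording that reaches the primary endpoint. Followed literally, the rules allow a late linezolid stop to be counted as treatment failure in someone then randomized as a favorable responder and kept in mITT. The effect is a modest pull toward no difference: with 5–10% affected, about 0.75 to 1.5 points off a 15-point excess. It is close to nothing if few participants are affected or if linezolid doses are counted alone.

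This rests on the enrolment clock, the plain reading of the failure definition, and an assumed share affected. It also assumes that Tables S2 and S7 and the two committees do not already deal with it. The documents do not show that such participants have been or will be randomized, only that the printed rules do not prevent it.

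**What to change.** 1. In Outcome measures, state that a linezolid reduction or cessation allowed under Treatment of patients, with the other drugs continued, is not by itself treatment failure. Report it under safety, where adverse events of grade 3 or higher are already an outcome.
2. For the randomized duration comparison, count only failure events that occur after the month-6 randomization. This also covers other adverse-reaction changes before month 6 that would still be failures, and it leaves FR-6 untouched, so no one is moved to nine months because of toxicity.

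The cost is two sentences and a slightly lower event rate. Recruitment was expected to run to December 2024, so both rules should be adopted before any comparison by duration arm. If Tables S2 or S7 already say this, bringing that wording into the main text is enough.
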